## Abstract

**Background:**

Rheumatoid arthritis is a chronic inflammatory disease, which affects 1% of the population. Hands and feet are most commonly involved followed by the cervical spine. The spinal column consists of vertebrae stabilized by an intricate network of ligaments. Especially in the upper cervical spine, rheumatoid arthritis can cause degeneration of these ligaments, causing laxity, instability and subluxation of the vertebral bodies. Subsequent compression of the spinal cord and medulla oblongata can cause severe neurological deficits and even sudden death. Once neurological deficits occur, progression is inevitable although the rapidity of progression is highly variable. The first signs and symptoms are pain at the back of the head caused by compression of the major occipital nerve, followed by loss of strength of arms and legs. The severity of the subluxation can be observed with radiological investigations (MRI, CT) with a high sensitivity.

The authors have sent a Delphi Questionnaire about the current treatment strategies of craniocervical involvement by rheumatoid arthritis to an international forum of expert rheumatologists and surgeons. The timing of surgery in patients with radiographic instability without evidence of neurological deficit is an area of considerable controversy. If signs and symptoms of myelopathy are present there is little chance of recovery to normal levels after surgery.

**Design:**

In this international multicenter randomized clinical trial, early surgical atlantoaxial fixation in patients with rheumatoid arthritis and radiological abnormalities without neurological deficits will be compared with prolonged conservative treatment. The main research question is whether early surgery can prevent radiological and neurological progression. A cost-effectivity analysis will be performed. 250 patients are needed to answer the research question.

**Discussion:**

Early surgery could prevent serious neurological deficits, but may have peri-operative morbidity and loss of rotation of the head and neck. The objective of this study is to identify the best timing of surgery for patients at risk for the development of neurological signs and symptoms.

## Background

Rheumatoid Arthritis (RA) is a chronic, systemic, inflammatory disease with an unknown etiology characterized by an erosive synovitis. Genetic and environmental factors play an important role. Both humoral and cellular immune responses are present. In caucasians the prevalence of RA is 0.8–1% [1] and the incidence is 27 per 100.000 of the general population [2]. The upper cervical spine shows signs of damage in 17–86% of patients with RA and is the most commonly involved structure after hands and feet [3]. The huge difference in the prevalence of cervical spine pathology is the result of absence of standardized international accepted definitions of subluxations of the atlantoaxial segment and inconsistent results in the literature. The use of better anti-inflammatory drugs in the last decade resulted in delayed and maybe a lower incidence of cervical spine involvement.

The spinal column consists of vertebrae stabilized by an intricate network of ligaments. Especially in the cervical spine, rheumatoid arthritis can cause degeneration of these ligaments, causing laxity, instability and subluxation of the vertebral bodies. Subsequent compression of the spinal cord and medulla oblongata can cause severe neurological deficits and even sudden death. Cervical spine involvement typically begins early in the disease process, and its progression has been closely correlated with the extent of peripheral disease activity [4-6]. Several types of subluxations have been described [3]. The first signs and symptoms of atlantoaxial instability are the result of rheumatoid synovial proliferation. Because of erosions of the transverse, apical and alar ligaments an anterior atlantoaxial subluxation (AAS) develops. Damage to the transverse ligament alone will allow approximately 3 to 4 mm of subluxation; a greater anterior atlanto dental interval (AADI) implies damage to the alar-apical ligament complex, an incomplete odontoid peg or a resorbed dens [4]. The average duration of RA at the onset of AAS has been reported being 12.7 years (3–26 years) [7]. Many patients acquire AAS in the first 3 years of their disease, but neurological impairments develop after a mean period of 18 years (range 4–50 years) [8]. When the odontoid process erodes a posterior AAS can evolve. Vertical Translocation (VT) (Cranial settling, basilar invagination, or superior migration of the odontoid process) results from progressive destruction of the lateral mass joints (atlantoaxial and occipitoatlantal) and the lateral masses themselves, as a result of chronic craniocervical instability [9-11]. The odontoid process moves towards and beyond the borders of the foramen magnum. Secondarily periodontoid pannus is formed in reaction to the chronic instability [3,12]. VT is observed in 4–35% of patients [13]. Because of VT the AADI can decrease, which virtually is a paradoxal improvement [9,14,15]. VT appears after a mean of 16.5 years (4–33 years) after the onset of the RA inflammatory process and almost exclusively after the onset of AAS [8,16]. Involvement of the subaxial spine (SAS) is less common, occurs later in the course of the disease, and manifests as multilevel anterior dislocation (7–29%) [13].

### Signs and symptoms

Clinical signs and symptoms as a result of AAS vary from asymptomatic to total incapacitation. Occipital pain, both from joint destruction and occipital nerve entrapment, and signs and symptoms of myelopathy are the most common complaints. Symptoms caused by instability are neck pain, headache and occipital neuralgia. As a result of medullary compression paresthesias, numbness, weakness, jactitations and sphincter disturbances can develop.

When VT is present with medullary compression the signs and symptoms can be dysarthia, dysphonia, dysphagia, diplopia, facial numbness (cranial nerve palsies), sleep apnea, and long tract signs. The long tract signs are difficult to assess, since the disability caused by progressive joint disease can obscure objective long tract signs such as hyperreflexia and spasticity. Severe compression of the medulla oblongata can result in vascular insufficiency leading to dizziness, vertigo and syncope. Vertebrobasilar ischemia is rare and occurs as a result of compression by the odontoid process [17,18]. VT can also give rise to cruciate paralysis and occasionally sudden death. The presence of symptoms is not correlated with the severity of radiological abnormalities.

### Natural history

The time interval between the existence of AAS and the development of neurological signs and symptoms varies widely [16,19-24]. A review by Bouchaud-Chabot [3] showed that at least 15% of the patients with radiological subluxation had no symptoms or signs. Progressive neurological deficits have been reported to be present in 15 to 36% of patients with RA [13]. If neurological deficits occur, spontaneous recovery can not be expected with conservative treatment and progression is inevitable and portends a poor prognosis [6,25-29]. About 50% of these patients die within 6 months and almost everyone dies within a few years after the first signs of myelopathy [2,25].

### Treatment

Generally accepted indications for atlantoaxial surgical fixation are severe C2 neuralgia and neurological deficits (Ranawat IIIA and IIIB) with signs and symptoms of myelopathy [13,14,16,30]. Surgical intervention is indicated to reduce and stabilize the craniocervical junction, preserve or restore neurological function and prevent further neurological deterioration [1,2,9,31-33]. However, there is no consensus or guideline when to operate on asymptomatic patients with radiological abnormalities. Some surgeons and rheumatologists prefer to operate in an early stage of the disease [34], others operate once neurological signs and symptoms have occurred [14]. Surgery in patients without neurological deficits is easier and less complex compared to patients with neurological impairments [9,32,34-36]. On the other hand loss of rotation occurs and there is a small risk of morbidity.

As a result of lack of evidence of the beneficial effect of surgery in an early stage of the disease, not all rheumatologists screen routinely for AAS as a result of the RA. Some rheumatologists screen patients with plain radiographs, others perform radiological investigations once patients present with complaints or neurological deficits.

Until the early 90's, the classical surgical approaches had a very high peri-operative morbidity and mortality rate. Since 1996, new surgical techniques with titanium instrumentation are used that are safer and make it possible to mobilize patients the first day after surgery [37-42]. In a study performed by Agarwal [7] no VT appeared after 'early' atlantoaxial fixation in patients with anterior AAS. Adjacent level involvement after occipitocervical fixation is approximately 7% in 3 years [43], this percentage is lower if only a C1C2 fixation has been performed.

The mortality rate of patients with myelopathy treated conservatively is very high. However, non ambulant quadriparetic patients who were operated on had a poor prognosis as well [2,9,27]. In a study performed by Casey and Crockard, the mortality rate of operated Ranawat IIIB patients was 58% within 3 years, compared to 20% of Ranawat IIIA patients [2]. The Class IIIB patients have unique management considerations in which surgery (despite high morbidity) often remains the best therapeutic option available. Improvement of even one grade in their Ranawat score from Class IIIB to Class IIIA brought about by surgery confers on them a huge benefit in terms of their quality of life and survival [9].

### The Delphi Trial – I(RCT)^2^

What is lacking from the literature is a prospective, rheumatoid population based study that gives information about the prevalence and progression of AAS, VT, or other important manifestations of RA involvement of the cervical spine. Because of the variable time interval between the existence of radiological atlantoaxial cervical spine involvement and the development of neurological deficits, it is not known when surgical fixation has to be performed. In the literature many authors suggest that a randomized clinical trial about the best timing of surgery in AAS as a result of RA has to be performed [1,2,9,11,34,43]. The objective of this study is to compare early surgery with prolonged conservative treatment for patients with rheumatoid arthritis and atlantoaxial cervical spine involvement without neurological impairments.

## Design

An international multicenter randomized clinical trial will be performed. Centers in the Netherlands (table 1), Belgium, Denmark, France, Germany, Italy, Latvia, Portugal, Spain, Sweden, Switzerland, United Kingdom, USA and Canada will participate (table 2 and figure 1 and 2). The multicenter design is necessary to recruit all patients in the inclusion period of 2 years. Early surgery will be compared with prolonged conservative treatment. The selection and randomization procedure is depicted in figure 3. The overall range for randomization of the AAS is an AADI between 5–12 mm. Participating centers/countries are allowed to randomize different intervals of subluxation. The intervals are predefined as 5–8 mm, 5–12 mm and 8–12 mm. Demographic and clinical data will be collected of each patient. The randomization of all patients will be performed centrally at the LUMC by the trial coordinator and datamanager by a concealed randomization list in random permuted blocks.

After a follow up of 5 years the main research question will be answered, although the total follow-up will be 10 years. Patients excluded from the trial will be followed in a cohort group and treated according to the usual care by surgical fixation or conservative treatment. The LUMC will function as the research and data coordinating center, where the data will be collected, analyzed and publications prepared. Eligibility criteria will differ from site to site, according to local perceptions of equipoise. These efforts will increase the generalization of the results. The authors have full access to the data, direct the data-analysis and are responsible for decisions regarding publication. The principal investigator and the trial coordinator assume full responsibility for the integrity and interpretation of the data.

### Main research questions

Null hypothesis; there is no difference in outcome between early surgical fixation and prolonged conservative treatment in patients with AAS with an AADI between 5 and 12 mm without neurological complaints. Because of the many uncertainties in the rheumatoid arthritis process the following research questions will be answered.

1. Does early surgery in neurological intact patients with RA and radiological signs of AAS result in less progression of C1–C2 subluxation and VT with or without complaints and neurological disability compared to prolonged conservative treatment?

2. Is early surgery more cost-effective than prolonged conservative treatment in this patient population?

During the explorative analyses the next questions will be answered.

3. Is it possible to define subgroups, which benefit most from one of the allocated treatment strategies?

### Patients

All patients with RA and atlantoaxial cervical spine involvement on conventional X-rays, CT or MRI of the cervical spine without neurological impairments will be asked to participate in the trial at one of the participating RA specialized hospitals. If patients with RA, aged 18–70 years old, have an AAS in the randomization range without neurological impairments (Ranawat I and II) without severe comorbidity, MRI incompatibility or previous cervical surgery, early surgical fixation will be compared with prolonged conservative treatment. The in- and exclusion criteria of the delphi trial are listed in table 3. Patients with neurological deficits as a result of cervical spine involvement will be followed in a cohort group.

### Sample size/power calculation

The sample size is calculated on the basis of the outcome difference during the follow-up period of at least 5 years. Hypothetically, 8% of included patients will worsen in the 5 year follow up period resulting in an event (Kaplan Meier) (16,21). In the early surgery group the event rate is expected to be 2% or less [44]. 2% is chosen because it has to be a save alternative to 'wait and see'. A two-sided log rank test with an overall sample size of 250 patients, achieves 90% power at a 0.05 significance level to detect a difference in groups 1 and 2 after 5 years of follow up. Patients enter the study during an accrual period of 2 years. 50% of the enrolment is complete when 50% of the accrual time has past. A follow-up period of 5 years with a 20% loss from group 1 and a 20% loss from group 2 is calculated.

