### Primary and secondary outcome parameters

***The primary outcome ***is the occurrence of an event. Events are defined as 1) neurological deficit, 2) radiological progression, 3) surgery, 4) resurgery, 5) death. (see table 5).

1). Neurological deficit is defined as a worsening in the Ranawat scale to IIIA or IIIB, or a deterioration of the MDI score >3 points. The Ranawat classification is a neurological classification and useful in evaluating patients, planning treatment and evaluating results. Class I patients have no neurological deficit, Class II patients have subjective weakness with hyperreflexia and dysesthesia. Class IIIA patients have objective weakness and long tract signs. Class IIIB patients are wheelchair bound or bedridden. The Ranawat classification fails to differentiate reliably between classes II and IIIA, the area of most clinical interest to the operating surgeon [45]. Casey and Crockard developed and validated the MDI according to the Stanford HAQ. The MDI consists of 10 functional questions. The more severe a patient has been disabled the higher the score [45].

2). Radiological progression is defined as an enlarged AADI of more than 12 mm, development of VT with impingement of the spinal cord or medulla oblongata, or signs of myelopathy. The Redlund Johnell method will be used to measure the severity of VT, which is the distance of the base of C2 to the palato-occipital line of McGregor (less than 34 mm in men and 29 mm in women) [11].

3). Incidence of surgery in the conservative treatment group. One of the goals of the conservative treatment is to avoid surgery for intolerable pain for example. The surgical rate is therefore an indication of the success or failure of the conservative treatment policy.

4). The incidence of resurgery at the cervical spine in the early surgery group will be an indication of the failure rate for surgery.

5). Death: all causes.

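### The stated 90% power does not follow from the protocol's own inputs: 250 patients in total give roughly 55–65% power for 8% versus 2% at the 5-year analysis

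*Protocol article*

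**What the plan says.** The Sample size/power calculation section of the protocol article gives a full set of inputs and a result.

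- Conservative arm: "Hypothetically, 8% of included patients will worsen in the 5 year follow up period resulting in an event".
- Surgery arm: "In the early surgery group the event rate is expected to be 2% or less".
- Test, size and power: "A two-sided log rank test with an overall sample size of 250 patients, achieves 90% power at a 0.05 significance level".
- Time frame: "the outcome difference during the follow-up period of at least 5 years". Also "Patients enter the study during an accrual period of 2 years", with enrolment evenly spread.
- Loss: 20% in each group.

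The abstract (Design) repeats the total: "250 patients are needed to answer the research question".

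The primary outcome is a composite of neurological deficit, radiological progression, surgery in the conservative group, resurgery in the surgery group, and "Death: all causes". The Statistical analysis section places main analyses at both 5 and 10 years.

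**The concern.** At 8% and 2%, the average event proportion over 5 years is 5%. So 250 patients yield about 12.5 events even with nobody lost. That is few for 90% power, even at a hazard ratio near one quarter.

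The main research question is to be answered at 5 years, against a null hypothesis of no difference. A non-significant result would be read on the strength of a 90% claim, which implies a 1 in 10 chance of missing the design effect. If true power is 56–63%, that chance is 37–44%. Sites and ethics reviewers asked to randomise neurologically intact patients to surgery also rely on this figure.

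**Working it through.** **Inputs.** From the sample-size section: 8% and 2% at 5 years, 250 in total, two-sided 0.05, 2-year uniform accrual, at least 5 years of follow-up, 20% loss per group. Assumed, because not stated: 1:1 allocation (125 per arm), exponential event times, and loss at a constant rate reaching 20% by year 5.

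**Step 1. Hazards.**
- h1 = −ln(0.92)/5 = 0.01668
- h2 = −ln(0.98)/5 = 0.00404
- HR = 0.00404/0.01668 = 0.242; ln HR = −1.4176
- Loss rate η = −ln(0.80)/5 = 0.0446

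**Step 2. Events needed for 90% power.** (1.960 + 1.2816)² = 10.51.
- Schoenfeld: 4 × 10.51/1.4176² = 20.9
- Freedman: 10.51 × [(1 + 0.242)/(1 − 0.242)]² = 28.2

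**Step 3. Events expected.** Per arm: 125 × h/(h + η) × [1 − exp(−(h + η)t)], averaged over the follow-up times t.
- Exactly 5 years each: 125 × 0.272 × 0.264 = 9.0, and 125 × 0.083 × 0.216 = 2.2; total 11.2
- 5 to 7 years (2 years of accrual plus 5): 10.45 + 2.62 = 13.1

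**Step 4. Power.** With E events:
- Schoenfeld: Φ(√E × 1.4176/2 − 1.96). At E = 13.1 this is Φ(0.60) = 72.7%.
- Freedman: Φ(√E × 0.610 − 1.96). At E = 13.1 this is Φ(0.25) = 59.7%.

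The log-rank test was also simulated directly (20,000 runs).

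**Step 5. Attempt to reproduce 90% with 250 in total.**

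| Follow-up, loss | Events | Schoenfeld | Freedman | Simulation |
|---|---|---|---|---|
| 5 years, none | 12.5 | 70.7% | 57.8% | 60.5% |
| 5 years, 20% | 11.2 | 66.1% | 53.3% | 55.7% |
| 5–7 years, none | 14.9 | 78.1% | 65.3% | 69.4% |
| 5–7 years, 20% | 13.1 | 72.7% | 59.7% | 63.1% |
| 3–5 years (5 years is total study time), 20% | 9.2 | 57.6% | 45.7% | 46.7% |

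A two-proportion comparison at 125 per arm without loss gives 58.6%. A one-sided test reaches at most 86.2% (Schoenfeld, 5–7 years, no loss). None of these readings gives 90%.

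**Step 6. What would give about 90%** (5–7 years, 20% loss).
- 8% versus 2% with 250 per group (500 in total): 90.9% by simulation, 87.7% Freedman, 95.2% Schoenfeld
- 125 per group with 11.5% versus 2%: 90.4% by simulation; 10% versus 2% gives about 82%

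**Step 7. The 10-year analysis.** With the same hazards, 250 patients and 10–12 years of follow-up, simulated power is about 84% if loss continues at 20% per 5 years, 88% if loss totals 20%, and 92% with no loss.

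**The case against.** **The 10-year analysis.** The protocol plans a second main analysis on the same event outcome, for which power would be about 84% on the same hazards and loss rate. This stands and limits the consequence: the trial as a whole is not confined to 56–63%. It does not rescue the sentence, which claims 90% after 5 years.

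**The surgery rate could be below 2%.** The text allows for this, but 2% is the design value: "2% is chosen because it has to be a save alternative to 'wait and see". At 1% versus 8% with no loss, Freedman gives 74.9% and two proportions 76.4%. Only Schoenfeld exceeds 90% (94.4%), and it falls to 88.8% with 20% fewer patients.

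**Method dependence.** The 56–63% is from simulation. With 20% loss at 5 or 5–7 years, the formulas span 53–73%. That range should be acknowledged; all of it lies well below 90%.

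**250 may be a per-group number.** A reader might infer this, since 250 per group gives roughly 90%. It is conjecture: the section calls 250 the overall size and the abstract repeats it.

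**Deaths dilute the contrast.** The 8% is described as patients who worsen, while the composite also counts all-cause death. A reader might infer that true power is lower still. The document does not support that. It ties both figures to the event, and the composite also counts surgery in the conservative arm only, which would widen the contrast. It gives no rate for either component, so the net effect on power cannot be fixed from it.

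**Truncation at 5 years.** The fixed 5-year row is one reading only. The section speaks of at least 5 years, and nothing in the article says that later follow-up is discarded.

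**Conclusion.** The point holds and needs correction. For 8% versus 2% at the 5-year analysis, 250 patients in total have about 56–63% power by direct simulation (53–73% across closed formulas with loss), and about 47% if 5 years is total study time. The stated figure is too high by about 27 to 34 points by simulation (90 − 63 and 90 − 56). The result rests on 1:1 allocation, exponential times and constant loss. Dropping the loss altogether and using the most favourable formula still gives only 78%.

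The error is confined to the claim for the 5-year analysis. The document supports neither a firm explanation of how it arose nor a further reduction for deaths.

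**What to change.** In the sample-size section, and correspondingly in the abstract:

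1. Replace the 90% claim with wording such as: 250 patients in total (125 per arm) give roughly 55–65% power for 8% versus 2% events at the 5-year analysis, and about 90% power only for about 11.5% versus 2% (5–7 years of follow-up, 20% loss).
2. Name the assumptions: 1:1 allocation, exponential event times, a constant loss rate reaching 20% by year 5, and whether follow-up is 5 years, 5–7 years or 5 years of total study time.
3. State that the shortfall concerns the 5-year analysis, and that the 10-year analysis would have about 84% power if the same hazards and loss rate continue.
4. Confirm that the 8% and 2% refer to the full composite primary event, including death in both arms and surgery in the conservative arm.
5. Check the source calculation. If 250 was a per-group number, say so.

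The cost is a change of wording and a less favourable stated power. Items 1 to 4 require no extra patients and touch no clinical rule.

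### The stated 90% power for 250 patients overall does not follow from the plan's own inputs; they give about 56–63%

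*Protocol article*

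**What the plan says.** The Sample size/power calculation section of the protocol article gives these design values:

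- Conservative arm: "8% of included patients will worsen in the 5 year follow up period resulting in an event".
- Early surgery arm: "In the early surgery group the event rate is expected to be 2% or less". The section fixes 2% as the design value: "2% is chosen because it has to be a save alternative to 'wait and see".
- Accrual: "Patients enter the study during an accrual period of 2 years", at a uniform rate ("50% of the enrolment is complete when 50% of the accrual time has past").
- Follow-up of 5 years, described at the start of the section as a minimum, with 20% loss in each group.

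The result drawn from them is "A two-sided log rank test with an overall sample size of 250 patients, achieves 90% power at a 0.05 significance level". The Abstract (Design) repeats the number as a requirement: "250 patients are needed to answer the research question". The article gives no allocation ratio, no number per arm and no time scale for the 20% loss.

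**The concern.** With rates this low, 250 patients produce very few events, and the power of a log-rank test depends on events. A simple count shows the problem: without any loss, 125 × 0.08 + 125 × 0.02 = 12.5 events at 5 years, which looks far too few for 90% power even at a large hazard ratio.

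The type II error is at stake. If the planning rates are exactly right, a power of 56–63% means that the trial misses the effect in about 37–44% of repetitions, where the plan allows 10%. The power figure is also the stated basis for 250 as the required number, so anyone weighing a non-significant result against it would overrate what the trial could show. Whether 8% and 2% suit the composite primary outcome is a separate question; both rates are taken as given here.

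**Working it through.** **Inputs from the Sample size/power calculation section:** 8% v 2% at 5 years; two-sided log-rank test at 0.05; 250 overall; 2 years of uniform accrual; 5 years of follow-up; 20% loss per group.

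**Assumptions added here:** 1:1 allocation (125 per arm), exponential event and loss times, and the 20% read as cumulative loss over 5 years.

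**Step 1: hazards per year.** Conservative: −ln(0.92)/5 = 0.01668. Surgery: −ln(0.98)/5 = 0.00404. Loss: η = −ln(0.80)/5 = 0.04463. Hazard ratio (HR) = 0.01668/0.00404 = 4.13; ln HR = 1.418.

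**Step 2: events needed for 90% power.**
- Schoenfeld: 4 × (1.960 + 1.282)² / 1.418² = 20.9.
- Freedman: (1.960 + 1.282)² × [(HR + 1)/(HR − 1)]² = 10.507 × (5.127/3.127)² = 28.2.

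**Step 3: events expected with 125 per arm.** The probability of an observed event by time t is λ/(λ + η) × [1 − exp(−(λ + η)t)]. For 5–7 years it is averaged over uniform entry.

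| Follow-up | Loss | Conservative | Surgery | Total |
|---|---|---|---|---|
| Exactly 5 years | none | 10.0 | 2.5 | 12.5 |
| Exactly 5 years | 20% | 9.0 | 2.2 | 11.2 |
| 5–7 years | none | 11.9 | 3.0 | 14.9 |
| 5–7 years | 20% | 10.5 | 2.6 | 13.1 |

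**Step 4: power at 250 overall.** With d events, Schoenfeld power is Φ(√d × 1.418/2 − 1.960) and Freedman power is Φ(√d × 3.127/5.127 − 1.960). For d = 11.2 these are Φ(0.41) = 66% and Φ(0.08) = 53%. With so few events and such a large hazard ratio the two formulas differ widely, so the log-rank test was also simulated directly (10,000 to 20,000 runs per case).

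| Follow-up | Loss | Schoenfeld | Freedman | Simulated |
|---|---|---|---|---|
| Exactly 5 years | 20% | 66% | 53% | 56% |
| 5–7 years | 20% | 73% | 60% | 63% |
| Exactly 5 years | none | 71% | 58% | 61% |
| 5–7 years | none | 78% | 65% | 69% |

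The stated 90% is not reproduced. The highest value in the table is 78%, from the most favourable formula with the loss ignored.

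**Step 5: relaxing single inputs at 250 overall, 20% loss kept (simulated).**
- Surgery rate 1% instead of 2%: 77% (exactly 5 years) to 84% (5–7 years).
- Follow-up of 10 years: 82%.
- Unequal 2:1 allocation, 5–7 years: 50% or 63%, depending on which arm is larger.
- One-sided test: 70–75%.

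**Step 6: what would give about 90%.**
- 250 overall, surgery rate 2%, 20% loss: a conservative-arm 5-year rate of about 11.5% (5–7 years) to 12.5% (exactly 5 years).
- 8% v 2% with 250 per arm and 20% loss: simulated power is 86% (exactly 5 years) and 91% (5–7 years).

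**The case against.** The strongest objection is that the section does not fix every input. Allocation and the time scale of loss are unstated, and follow-up appears both as 5 years and as a minimum of 5 years. The 56–63% therefore rests on named assumptions and is not the only possible figure. This stands, and the fix should name them. It does not rescue the 90%: unequal allocation does not raise the power, and reading the 20% as loss per year lowers the closed-formula results to about 39–53%.

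A second objection is that some readings do reach 90% with 250 in total. If the 8% is a pooled rate over all included patients, then with 2% in the surgery arm the conservative rate is 2 × 8% − 2% = 14%. If the 2-year accrual also lies inside a 5-year total, so that each patient has 3–5 years, simulated power is about 89–90%. This works numerically, so 90% at 250 overall is not impossible on every reading. But it needs a 14% rate printed nowhere and contradicts the section's own minimum follow-up of 5 years. With that follow-up kept, the same rates overshoot, at about 94–98%. Schoenfeld's formula with a 1% surgery rate and crude removal of 20% of patients gives 89%, but that departs from the chosen 2%, and Freedman gives 65% there.

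A reader might infer that 250 is a per-group number misprinted as a total. The arithmetic allows this but does not establish it: 250 per arm gives 91% only with 5–7 years of follow-up and 86% at exactly 5 years, and both the section and the Abstract present 250 as the total.

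A reader might also infer that a non-significant result will be reported as showing no difference. The article does not say so, and its Statistical analysis section already plans 95% confidence intervals for the group difference.

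**Conclusion.** The point holds. On the plain reading of the section, 250 patients overall give about 56% power at exactly 5 years and about 63% with 5–7 years of follow-up, against the stated 90%. Expected events are about 11–13 against the 21–28 needed. The figures rest on 1:1 allocation, exponential times and 20% cumulative loss over 5 years. The direction does not depend on the method: closed formulas give 53–73% with loss and at most 78% without. The source of the error cannot be settled from the article.

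**What to change.** In the Sample size/power calculation section, keep 250 overall and do one of two things:

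1. Replace the 90% by the power that 250 delivers at 8% v 2%, about 56–63%, naming the allocation ratio, the time scale of the 20% loss and whether follow-up is exactly 5 years or runs to 5 years after the last entry.
2. State the contrast for which 250 overall has about 90% power: about 11.5% (5–7 years) to 12.5% (exactly 5 years) v 2% at 5 years, under the same named assumptions.

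Then bring the Abstract's statement that 250 patients are needed into line.

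The cost is a less favourable power statement. The fix asks for no extra enrolment and no change in conduct. Declaring 250 per group would not be a rewording: it would double the trial to 500, and it is not proposed here.
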